#### Qualitative Analysis

For qualitative data using NVivo Software, an inductive content analysis will be executed to determine common themes [42]. This methodology supports a holistic and rich description of data, ideally suited to address project goals. This analysis will be grounded in an intersectional feminist framework [43]. This framework emphasizes that gender-based violence needs to be understood within the context of how identity and social location intersect and interact and how systems of power, oppression, and privilege shape women’s lives [44,45]. Analysis will take place at the end of data collection and will be conducted independently and simultaneously by 2 investigators and a research assistant. NVivo software will support analysis through coding and providing a comprehensive data management system. Each coder will become immersed in the data and once saturation is reached coding will commence [46]. Initially, open coding data line by line will be used and when themes emerge they will be organized into similar topics and then categories. Each category will be examined to determine meaning and will be assigned a working name and flexible definition. Axial coding will then be completed by recontextualizing the data that was coded into each category to determine consistency within the category (to decrease human bias in selective coding). Lastly, the categories will be re-examined to finalize the name and definition as well as to ascertain the underlying meaning of the theme within the context of the findings. Once each coder is finished coding, findings will be compared to ascertain if there is agreement on major emergent themes. If there is no agreement, a majority will be used to classify major themes.

### Power

#### Cohort 1

A sample of 20 women was selected as this is a feasibility study and it is anticipated we will reach saturation (assessed by the sole interviewer with the use of field notes) in the qualitative data [46]. This sample will be used to inform future power analysis for the large-scale RCT.

#### Cohort 2

One hundred charts will be audited (50 from each of the two arms, the intervention and standard care arms). This sample size, for this feasibility study, was selected as it will allow us to extend the breadth and depth of analysis from cohort 1. This ultimately enhances the validity of the study’s findings [31] by contextualizing the differences between the intervention and standard care, therefore contributing to valuable knowledge translation.

## Results

The work reported here is in the proposal phase. Once the protocol is implemented, we will report the results in a follow-up paper. However, we hypothesis that PCNS-delivered CBT will result in decreased PTSD, anxiety, and/or depression symptomatology, and improved maternal-infant attachment, coping, and QOL. We also hypothesize this study will be feasible in terms of fidelity and deliverability, as well as be highly acceptable to participants.

## Discussion

### Study Rationale and Future Direction

We hypothesize that PCNS-delivered CBT will be effective in treating PTSD symptomatology, depression and anxiety disorders affecting the sample of pregnant women selected [47], thereby contributing to participants’ improved QOL and maternal-infant attachment, and positive child health outcomes following birth.

The PATH study serves to build upon existing health literature that explores the positive impact of CBT for survivors of IPV and those experiencing mental health challenges [48-50] within periods of transformational change associated with pregnancy, childbirth, and motherhood. This feasibility study will help to address a current lack of literature in the area by filling a gap in intervention research aimed at improving the health and QOL of perinatal women who have experienced IPV and have symptomology consistent with PTSD, depression and/or anxiety.

Furthermore, successful implementation will help to determine the feasibility and acceptability of the study methodology and protocol, to support the future full-scale RCT. Efficacy will be determined in relation to a reduction in PTSD, anxiety, and depressive symptoms, and improvement in maternal-infant attachment, maternal coping, and maternal QOL. Feasibility will be assessed in relation to fidelity and resource allocation (from the provider, participant, and system perspectives) and acceptability will be measured in terms of perceived value from the participants’ perspective.

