**Methods:**

The Promoting Attachment Through Healing (PATH) study will use a mixed-methods approach grounded in an intersectional feminist framework to explore the effectiveness of trauma-informed CBT for pregnant survivors of IPV. Study participants will be recruited through the hospital-based Perinatal Mental Health Clinic (London, Ontario, Canada). A feasibility sample of 20 pregnant women (cohort 1) will be selected to engage in an eight-session antenatal CBT intervention facilitated by the program’s perinatal clinical nurse specialist, with evaluation at baseline, at two months postpartum (intervention and online questionnaire), and at six and twelve months postpartum (online questionnaire only). Concurrently, we will conduct a retrospective audit of 100 medical charts (cohort 2; 50 charts of perinatal women who received CBT and 50 charts of women who did not receive perinatal CBT) from the past five years. The efficacy of the intervention will be based on a reduction of mental illness symptomatology, improved maternal-infant attachment, maternal coping, and maternal quality of life. Additionally, the feasibility of the protocol and acceptability of the intervention from the women’s perspective will be examined. Inductive content analysis of all qualitative data will be used to determine common themes. Additionally, descriptive statistics, including measures of central tendency and dispersion, will be computed for all continuous variables. Alternatively, frequency tables will be constructed for all categorical variables.

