**Conclusions:**

Findings will assess the acceptability of the study methodology and protocol for a full-scale randomized controlled trial. Furthermore, if CBT is proven effective for pregnant survivors of IPV, this intervention could be readily adopted by health care and social support services, thereby contributing to an improved standard of care for this unique population.

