### Participant Inclusion Criteria

#### Cohort 1

Inclusion criteria include: 1) English-speaking; 2) pregnant women (any gestational age); 3) living in Ontario; 4) attending the Perinatal Mental Health Clinic at the recruiting hospital; 5) a history of IPV (disclosed to the PCNS during their intake assessment); and 6) symptomatology consistent with PTSD, depression, or anxiety that adheres to the diagnostic criteria outlined in the Diagnostic and Statistical Manual of Mental Disorders (DSM)-V (as assessed by the PCNS at intake).

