### Conclusions

This is the first intervention research of its kind examining the impact of perinatal CBT for women who have experienced IPV with mental illness. If the hypotheses of this research are correct, then not only would that support the scale-up of the intervention, it could also have far-reaching implications for individuals and society. Specifically, the findings would not only benefit individual participants and their families in terms of strengthened maternal-infant bonds and family units, but may also result in broader societal benefits, including reduced chronic health care utilization and associated treatment costs, as well as increased productivity, participation, and economic contribution within the London community [51,52].

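### Efficacy is to be read from a fall in symptom scores, but the only repeated scale data come from 20 CBT-treated women selected for symptoms, and the standard-care charts, as listed, cannot supply a contrast on those scales

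*Protocol article*

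**What the plan says.** - **Efficacy criterion.** Discussion, Study Rationale and Future Direction: "Efficacy will be determined in relation to a reduction in PTSD, anxiety, and depressive symptoms". The sentence goes on to improvement in attachment, coping and quality of life. The Abstract's Methods paragraph agrees: "The efficacy of the intervention will be based on a reduction of mental illness symptomatology". Neither sentence names a comparator, threshold or test.
- **Who is measured.** Cohort 1 has 20 women, all receiving CBT. Eligibility requires "symptomatology consistent with PTSD, depression, or anxiety that adheres to the diagnostic criteria", "as assessed by the PCNS at intake". Scores are taken at baseline in pregnancy (T1) and at 2, 6 and 12 months postpartum (T2 to T4).
- **Named comparator.** Methods, Design sets up 50 CBT charts and 50 standard-care charts as cohort 2. Statistical Analysis plans generalized estimating equations (GEE) for change over time and for the contrast with standard care.
- **What cohort 2 supplies.** Data Collection, Cohort 2 describes one extraction per chart with no patient contact. It lists diagnosis and treatments, general health status, obstetric and birth data, chart evidence of coping and attachment, and newborn data.
- **Use of the result.** Abstract, Conclusions: "if CBT is proven effective for pregnant survivors of IPV, this intervention could be readily adopted by health care". Discussion, Conclusions says that if the hypotheses are correct, "not only would that support the scale-up of the intervention". Power, Cohort 1: "This sample will be used to inform future power analysis for the large-scale RCT".
- **Limitations.** The section lists small sample, single recruiting site and reliance on one CBT provider.

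**The concern.** Women who enter because their symptoms are high at intake will, on average, score lower later even if treatment does nothing, provided the later score is less closely related to the selecting assessment than the baseline score is. Two other influences act over the same period: the passage from pregnancy to postpartum, and the social work or psychiatry referral that Methods, Design describes for women who screen positive. A within-cohort change cannot separate any of these from CBT.

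A control measured on the same scales at the same times would deal with this, but the listed cohort 2 data do not provide one. The Limitations section asks whether a result would be due to the intervention or to the person delivering it. It does not consider that it might be due to neither. At stake is what the pilot may conclude: a fall in scores could be read as efficacy, linked to adoption and scale-up, and possibly carried into the sizing of the RCT.

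**Working it through.** **1. Can the standard-care contrast be made on the symptom scales?**

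| | Cohort 1 | Cohort 2 (both arms) |
|---|---|---|
| Source | Interviews and questionnaires | One chart extraction, no contact |
| PCL-5, EPDS, STAI | Yes | Not listed |
| 2, 6 and 12 months postpartum | Yes | Not listed |
| Standard-care group | No | 50 charts |

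The scales and the standard-care women are in different cohorts. As listed, GEE has symptom scores over time for CBT-treated women only.

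**2. How large could regression to the mean be?**

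The plan gives no SD, correlation, alpha or effect size, so there is no figure of its own to reproduce. From the documents: n = 20, selection on symptoms at intake, baseline before CBT. Assumed: normal scores; the top 50%, 30% or 20% on the intake assessment are eligible; correlations as in the table, with the T1-T2 correlation equal to the intake-T2 correlation; two-sided 5% paired t-test; zero treatment effect; 8,000 simulated studies per setting.

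Expected fall in SD units = i x (r[intake,T1] - r[intake,T2]), where i is the mean of the selected part of a standard normal: 0.80, 1.16 and 1.40 for the top 50%, 30% and 20%.

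Examples:
- T1 is the selecting measure, r = 0.8, top 50%: 0.80 x (1 - 0.8) = 0.16 SD.
- T1 is the selecting measure, r = 0.5, top 20%: 1.40 x (1 - 0.5) = 0.70 SD.
- T1 separate, correlations 0.8 and 0.5, top 20%: 1.40 x 0.3 = 0.42 SD.
- T1 separate, correlations 0.7 and 0.6, top 30%: 1.16 x 0.1 = 0.12 SD.

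| Case | r(intake,T1) | r(intake,T2) | Expected fall (SD) | Mean falls | Significant fall |
|---|---|---|---|---|---|
| a. T1 is the selecting measure | 1 | 0.5-0.8 | 0.16-0.70 | 87-100% | 19-91% |
| b. T1 separate, close to intake | 0.8 | 0.5-0.6 | 0.16-0.42 | 79-98% | 12-46% |
| c. T1 separate, slightly closer than T2 | 0.7 | 0.6 | 0.08-0.14 | 66-75% | 6-10% |
| d. Equal correlations | 0.6 | 0.6 | 0 | about 50% | about 2.5% |

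With 15 women (25% lost, assumed), the significant rates in case a are 16-81%. Natural course and referral are not modelled.

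**3. What if the observed change were used as the RCT effect size?**

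The plan does not say it will be, so this step is conditional. At 80% power and two-sided 5%, n per arm = 2 x (1.96 + 0.84)^2 / d^2, about 15.7 / d^2.

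- True d = 0.5 inflated by 0.3 to 0.8: 25 per arm instead of 63. Power at d = 0.5 is Phi(0.5 x sqrt(25/2) - 1.96) = Phi(-0.19), about 42%.
- True d = 0.3 inflated by 0.3 to 0.6: 44 per arm instead of 175. Power at d = 0.3 is Phi(0.3 x sqrt(44/2) - 1.96) = Phi(-0.55), about 29%.

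**4. What 20 women can support.**

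The 95% CI for mean change has a half-width of 2.093 / sqrt(20) = 0.47 SD of change. An SD from 20 women has a 95% CI of 0.76 to 1.46 times its estimate (chi-square, 19 df).

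**The case against.** The strongest reply is that the plan does have a control. It names 50 standard-care charts, from women who would have been eligible but were not referred, and it plans a GEE contrast with them. A reader might infer from cohort 1 alone that there is no control; the documents do not support that. What stands against the plan is narrower: the named control does not, as listed, carry the scales or the time points. Some doubt remains, because the abstraction instrument is not shown and the list includes general mental health status.

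A reader might also infer that regression to the mean would usually yield a significant result. That requires the T1 score to be the selecting measure and a paired test to be the rule, and the plan states neither. Selection is by the nurse specialist's assessment on any one of three conditions, which dilutes regression on each separate scale. Cases b to d are therefore as admissible as case a.

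It is tempting, too, to say the RCT will be underpowered. The Power section says only that cohort 1 will inform the power analysis. Taking the SD, correlation or retention from it would not import an inflated effect.

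Finally, the stated goal is to explore efficacy in a pilot, the adoption and scale-up sentences are conditional, and Limitations does voice doubt about scale-up. This is fair and lowers the severity. It does not cure the efficacy sentences, and the condition attached to scale-up is that the hypotheses are correct. Those hypotheses include a decrease in symptoms, which other causes could also produce. Nor do the documents say which way symptoms move after birth; the Background describes postpartum care as a possible source of distress, so that influence could run either way.

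**Conclusion.** The point holds in this form: efficacy is tied to a symptom reduction, and the only repeated scale data on which to judge it are an uncontrolled change in 20 women selected for symptoms. The standard-care contrast cannot be made on those scales from the data listed, and Limitations mentions neither regression to the mean nor the lack of a usable concurrent control.

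The size is uncertain. With no CBT effect, the literal criterion (a reduction on a given scale) would be met in about 50-100% of studies. A significant fall would occur in about 2.5% with no differential correlation, 6-46% if T1 is separate from intake but closer to it than T2, and 19-91% if T1 is the selecting measure. All of this rests on assumed correlations and selection shares. The RCT power figures of 29% and 42% are illustrations that apply only if the raw change becomes the effect size.

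This should be fixed, because it changes what the pilot may conclude. It does not touch the feasibility and acceptability aims.

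**What to change.** 1. **Abstract (Methods) and Study Rationale.** Replace the efficacy criterion with: *Cohort 1 estimates within-woman change with 95% confidence intervals; this change will not be interpreted as efficacy of CBT.*
2. **Abstract (Conclusions) and Discussion (Conclusions).** Remove proof of effectiveness, adoption and scale-up as consequences of this pilot. State that the decision it serves is whether to proceed to an RCT.
3. **Statistical Analysis and Data Collection, Cohort 2.** Reconcile the two by limiting the standard-care contrast to outcomes actually abstracted in both cohort 2 arms.
4. **Limitations.** Add regression to the mean and the absence of a usable concurrent control for the symptom scales.
5. **Power, Cohort 1.** Limit what cohort 1 contributes to the RCT power analysis to the SD (with its uncertainty), the within-woman correlation and retention. Set the RCT effect size on a minimal important difference, not on the observed change.

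The cost is wording only, with no new data or visits. The price is a less favourable headline claim.

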### Limitations

The proposed study is not without limitations, namely the small sample size, limited recruiting methodology, and high reliance on the PCNS who is delivering CBT at the recruitment site. The small sample size chosen for this feasibility study is a limiting factor for statistical analyses as well. The fact that recruiting is limited to a single site could also be problematic as this significantly decreases the pool of potential participants. Finally, the high reliance on the PCNS who is delivering CBT at the recruitment site also limits the pool of participants, in addition to potential concerns regarding scale-up and reproducibility of the intervention. While having one intervention decreases the variability in terms of consistent delivery of the intervention, it speaks to a potential difficulty in ascertaining if the results were due to the intervention alone or the intervention/interventionist.

### Conclusions

This is the first intervention research of its kind examining the impact of perinatal CBT for women who have experienced IPV with mental illness. If the hypotheses of this research are correct, then not only would that support the scale-up of the intervention, it could also have far-reaching implications for individuals and society. Specifically, the findings would not only benefit individual participants and their families in terms of strengthened maternal-infant bonds and family units, but may also result in broader societal benefits, including reduced chronic health care utilization and associated treatment costs, as well as increased productivity, participation, and economic contribution within the London community [51,52].

## Appendix

Multimedia Appendix 1 Peer-reviewer report.

## Abbreviations

Apgar score: Appearance, Pulse, Grimace, Activity, and Respiration score
CBT: cognitive behavioral therapy
DSM-V: Diagnostic and Statistical Manual of Mental Disorders—Fifth Edition
EPDS: Edinburgh Postnatal Depression Scale
IPV: intimate partner violence
LHSC: London Health Sciences Centre
MAI: Maternal Attachment Inventory
PATH: Promoting Attachment Through Healing
PCI: Proactive Coping Inventory
PCL-5: PTSD Checklist for DSM-5
PCNS: perinatal clinical nurse specialist
PTSD: posttraumatic stress disorder
QOL: quality of life
RA: research assistant
RCT: randomized control trial
STAI: State-Trait Anxiety Inventory
WHOQOL-BREF: World Health Organization Quality of Life Brief Assessment
